## Abstract

**Background:**

Treatment failure and disease relapse among tuberculosis (TB) patients are commonly caused by non-adherence. It can lead to prolonged infection, increased transmission, drug resistance, and loss of life. Even though the causative microorganism of TB has been identified for more than a century, the disease is still a substantial public health problem worldwide. This research aims to devise, implement, and assess an educational intervention to improve adherence to TB treatment.

**Methods and findings:**

A randomised clinical trial involving 146 Sudanese TB patients will be conducted at the Abu Anga hospital in Khartoum. The participants will be randomly assigned to the intervention and control groups. A 2-hour session will be offered to the intervention group in a one-day TB educational intervention course. The same educational materials will also be provided to the control group after the randomised controlled trial (RCT). Data will be collected at baseline, one month, and four months after the intervention. The primary outcome of interest is TB treatment adherence, while secondary outcomes include quality of life score, tuberculosis knowledge, and health belief domains. Generalised estimating equations (GEE) in SPSS software version 25.0 will be utilised to evaluate the changes over time.

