### Sample size

The sample size is calculated using the standard sample size estimate for an individually randomised design. Sample size will be determined according to the primary dependent variable (TB treatment adherence). The formula to calculate the difference between two population proportions will be used (power = 0.80, alpha = 0.05 two‐sided, P_1_ = estimated proportion (larger) P1 = 0.82, P_2_ = estimated proportion (smaller) P2 = 0.69) [22].

$$N=\frac{\{1.96\sqrt{2\times 0.33(1-0.33)}+0.842\sqrt{0.82(1-0.82)+o69(1-0.69)}{\}}^{2}}{{\left(0.82-0.69\right)}^{2}}.$$

N = 171 for each group.

By taking into account a 10% attrition rate, a total sample size of 188 (171 + 17 = 188) participants will be required for each group, giving a total sample size of 376 participants.

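### The Abstract sets the trial at 146 patients and the Sample size section at 376; at 146 the planned 80% power would be about 41–45%

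*Protocol article*

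**What the plan says.** The Abstract, under Methods and findings, gives the size of the trial: "A randomised clinical trial involving 146 Sudanese TB patients will be conducted at the Abu Anga hospital in Khartoum".

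The Sample size section bases the calculation on the primary outcome, treatment adherence, compared as two proportions. Its inputs are "power = 0.80, alpha = 0.05" (two-sided), "estimated proportion (larger) P1 = 0.82" and "estimated proportion (smaller) P2 = 0.69". It reports "N = 171 for each group" and then allows for losses: "By taking into account a 10% attrition rate, a total sample size of 188 (171 + 17 = 188) participants will be required for each group". For both groups together, the section puts the figure as "giving a total sample size of 376 participants".

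The Randomisation paragraph specifies 1:1 allocation, so 146 patients means 73 per group.

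**The concern.** Two totals are given for one trial, and they differ by a factor of 2.6 (376/146). The figure of 146 is not the total to be randomised (376), the evaluable total (2 × 171 = 342) or a per-group figure (171 or 188). The article does not call it a pilot, a subset, an interim count or a revised target. The only other samples mentioned are the seven and ten patients used to try out and face-validate the translated materials.

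The target decides when recruitment stops and is the yardstick for judging the finished trial. If recruitment stopped at 146, the power statement would not describe the trial that was run, and a null result on adherence would say little about the effect it was planned on. If 376 is the target, a reader of the Abstract could take a trial stopped at 146 as complete, or one that reached 376 as heavily over-recruited.

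**Working it through.** **Inputs.** From Sample size: p1 = 0.82, p2 = 0.69, difference 0.13, two-sided alpha 0.05 (z = 1.96), power 0.80 (z = 0.842), attrition 10%. From the Abstract: 146 in total. From Randomisation: 1:1 allocation.

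**Step 1: reproduce the plan's figure.** The pooled two-proportion formula is

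n = {1.96·√[2·p̄(1 − p̄)] + 0.842·√[p1(1 − p1) + p2(1 − p2)]}² / (p1 − p2)²

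with p̄ = (0.82 + 0.69)/2 = 0.755.

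- √(2 × 0.755 × 0.245) = 0.6082; times 1.96 = 1.1921
- √(0.82 × 0.18 + 0.69 × 0.31) = 0.6012; times 0.842 = 0.5063
- n = (1.1921 + 0.5063)² / 0.0169 = 2.8845 / 0.0169 = 170.7, so 171 per group

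This matches the plan. Adding 17 gives 188 per group and 376 in total, as stated.

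The formula as printed has 0.33 where p̄ should stand. Taken literally, that gives about 194 per group, so the stated 171 must have come from 0.755 (or its complement, 0.245). The 0.33 looks like a misprint, and it moves the requirement further from 73.

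**Step 2: power at each size.** The same formula solved for power is

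Power = Φ{[0.13·√n − 1.1921] / 0.6012}

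| Evaluable per group | 0.13·√n | z | Power |
|---|---|---|---|
| 73 (146 in total, no loss) | 1.1107 | −0.135 | 44.6% |
| 66 (146 less about 10%) | 1.0561 | −0.226 | 41.1% |
| 65 (146 less about 10%) | 1.0481 | −0.240 | 40.5% |
| 171 (plan) | 1.7000 | 0.845 | 80.1% |

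Ten percent off 73 leaves 65.7, hence the rows for 65 and 66.

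**Step 3: does the answer depend on the formula?** With unpooled variance, power is 45.5% at 73 and 41.9% at 66. Exact enumeration of the uncorrected chi-square test gives 44.7% and 41.1%. With a continuity correction the exact figures are lower, 37.4% and 34.1%. With the printed 0.33 in place of 0.755, the formula gives 37.4% and 34.0%. No variant comes near 80%.

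**Step 4: what 146 could detect.** Holding the smaller proportion at 0.69, 80% power needs the larger to be about 0.88 at 73 per group, or about 0.89 at 65–66 per group. That is a difference of about 19–20 points, against the 13 planned.

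**The case against.** The strongest reply is that the only worked and justified target in the article is 376, and the 80% power is attached to that target and never to 146. If 146 is a leftover or a slip in the Abstract, the design is sound and the defect is one wrong number in a summary. This stands as a limit on the finding: the power loss applies only if 146 is the operative target. It does not remove the contradiction, because the document gives no means of telling which figure is in force.

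A second reply is that 41–45% belongs to a simple comparison of two proportions. The Statistical analysis section plans generalised estimating equations over repeated assessments, with adjusted regression, and the primary outcome is a 10-item scale for which no adherence cut-off is given. That is fair. The figures are a like-for-like reading of the plan's own calculation and should be labelled as such; they are not the power of the planned models.

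Two smaller points also stand. The registered sample size is not in the document, so nothing can be said about it beyond advising a check. And adding 10% instead of dividing by 0.9 (188 against 190 per group) is a separate and immaterial matter: 188 × 0.9 leaves about 169 evaluable per group, with power 79.6%.

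**Conclusion.** The concern holds. The article gives two incompatible totals, 146 and 376, for the same individually randomised trial, and nothing in it reconciles them. The derived 171 per group is correct for the stated inputs, while 146 is 39% of the total that section requires.

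If 146 is the target, power for 0.82 against 0.69 at two-sided 0.05 is 44.6% without losses and about 41% after 10% attrition, so on that calculation the trial would more likely than not miss the effect it was planned on. If 376 is the target, the planned power stands and the Abstract is wrong by 230 patients. These power figures assume 1:1 allocation, the protocol's two proportions and an uncorrected two-proportion test. The contradiction itself rests on no assumption. It must be fixed, because it concerns the size of the trial and the power for its primary outcome.

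**What to change.** The sponsor should confirm which total is in force and state it identically in the Abstract and in Sample size.

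- **If the derived target is in force:** replace 146 in the Abstract with the total from Sample size (376 as written).
- **If 146 is in force:** remove the 80% power statement. Report that, on the two-proportion calculation for 0.82 against 0.69, power is about 41–45% depending on attrition, and that the difference detectable with 80% power is about 19–20 points. Say why the smaller number was chosen.

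In the same edit, correct the 0.33 in the printed formula to the value that yields 171, and check that the registry record carries the same total. The first option costs one number in the Abstract. The second costs a less favourable power statement. Neither needs a new procedure or new data.

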**Conclusions:**

This trial will provide information that could be used in improving TB control strategies to achieve better results in the adherence of healthcare services to the norms of the National Program and patient adherence to the disease treatment and cure.

**Trial registration:**

This study is registered at TCTR: (TCTR20210607006).

## Introduction

Tuberculosis (TB) is one of the top ten leading causes of fatalities globally. In 2017, TB was the identified cause of 1.6 million fatalities, particularly in developing countries. It also surpassed HIV/AIDS as the primary cause of death among single infectious agents [1]. TB continues to afflict millions of people annually. World Health Organisation (WHO) estimated that around 10 million people contracted TB in 2020; of these, 5.6 million were men, 3.3 million were women, and 1.1 million were children [2]. The national incidence rate of TB varies from fewer than 5 to above 500 cases of new and relapsing patients for every 100 000 people annually. In 2019, less than half of 54 countries recorded a low TB incidence rate [3]. TB remains a worldwide public health concern as the Tubercle bacillus is likely to have infected one-third of the global population. These people either suffer from the disease or are at risk of progressing to active disease status [4]. Even though the causative bacteria of TB had been identified more than a century ago and effective management strategies, including anti-TB drugs and vaccines, are available, it remains a substantial public health concern worldwide [5]. Treatment failure and disease relapse are commonly caused by non-adherence to treatment, resulting in higher infection rates, transmission, drug resistance, and deaths. A vital component of the WHO-recommended anti-TB strategy is Directly Observed Therapy (DOT). TB patients must take their medication under direct observation of health workers or family members [6]. This strategy is effective in improving treatment adherence. Nevertheless, the coverage rate of DOT is still low in some resource-poor countries and thus fails to improve treatment adherence in those countries [7].

Furthermore, this method requires a substantial investment of time from health workers or commitment from family members. Besides, it can be a financial burden and discourages patient autonomy [8]. As a result of these factors, DOT implementation has been largely restricted. A Chinese study discovered that DOT was only practised by 14% of patients, and worse still, the follow-up loss amounted to 28% [7]. Therefore, an innovative approach needs to be devised to innovate TB therapy. Poor adherence to treatment and failure to follow up raise mortality, morbidity, and the risk of drug resistance development, which can result in the prolonged spread of TB [9].

In Sudan, civil war in certain areas and people’s displacement while searching for a better life are among the various factors currently faced by Sudan, which may lead to the increase in the occurrence and spread of many health hazardous diseases, among them are TB infection and TB treatment adherence [10]. Sudan has adopted the DOTS strategy since 1993. However, failure to adhere to TB treatment continued among some patients, eventually resulting in their default of the treatment before completing it, despite health authorities’ efforts to address this issue [11]. To improve the treatment adherence level, various intervention methods have been designed and implemented across the world [12–14]. As recommended in the WHO End TB Strategy 2017, a set of novel interventions can be employed to raise adherence, such as sending text messages to cell phones, applying digital monitors to keep track of pill containers and medication consumption, as well as providing supportive treatment supervision by treatment partners [15].

In the literature, one of the methods that have been proven to have a positive effect on TB treatment compliance is an intervention based on the enhanced TB adherence model with a focus on empowering both patients and professionals [16]. Various theories and models have been implemented to increase adherence to TB treatment. For example, the Health Belief Model (HBM) is commonly applied as the theoretical framework of many educational interventions. Studies have proven the effectiveness of HBM in improving adherence to TB treatment [17,18]. Similarly, many studies that used educational intervention to improve TB treatment adherence among TB patients have been carried out globally [19,20].

Generally, studies on TB-focused interventions are scarce among newly diagnosed patients, especially in Sudan. Therefore, this study protocol aims to outline the development and implementation of an HBM-based educational intervention in an RCT as a means to educate TB patients in Khartoum, Sudan. Apart from that, this study also assesses the impact in terms of their TB knowledge, health beliefs, and quality of life (QOL). The study hypothesises that at the 1- and 4-month assessments, TB patients in the intervention group will show a raised score in the following areas:

TB treatment adherence level.TB knowledge scores.TB adherence to health beliefs (perceived susceptibility, perceived seriousness, perceived benefits, perceived barriers, confidence, and health motivation).QOL.

This research aims to devise, implement, and assess an educational intervention to improve adherence to TB treatment among TB patients in Sudan. We hypothesise that an educational module intervention based on the HBM will improve tuberculosis treatment adherence level, health beliefs, QOL, and knowledge among TB patients in Sudan.

## Materials and methods

### Study design

This randomised controlled trial (RCT) will be conducted in a parallel approach using one control group and one intervention group. The group members will include patients diagnosed with pulmonary TB based on the National Treatment Guideline under the Directly Observed Therapy (DOT) strategy. The participants will not be aware of the group assignments (single-blind). The educational material will be given to the intervention group after baseline data collection, while the control group will receive the educational material at the end of the study. Assessments will be carried out at baseline, one month, and four-month post-intervention, as shown in Fig 1.

**Fig 1 pone.0277888.g001:**
[figure not shown]
SPIRIT schedule of enrolment, interventions, and assessments [21].

### Conceptual model

This trial is grounded on the Health Belief Model (HBM), which focuses on the assessment of an individual’s health behaviour performed by examining perceptions and attitudes that someone may have towards disease and the negative outcomes of certain actions [21]. Fig 2 below depicts the conceptual model adapted from the health belief model.

**Fig 2 pone.0277888.g002:**
[figure not shown]
The conceptual model was adapted from the HBM [22].

### Study setting

The study will be based at the Abu Anga regional referral hospital in Omdurman city, Khartoum state, Sudan, which acts as Sudan’s primary TB specialist hospital. All cases of suspected resistant TB are sent to this facility when confirmation is needed. The hospital also provides healthcare services to the people of Khartoum and neighbouring states and cares for suspected TB cases.

### Study participants

Permission will be sought from the hospital authority to allow the research team to collect the information from TB patients. The team will meet the patients during their normal follow-up to introduce the study. The subject will be an individual Sudanese patient with TB aged 18 years and above who were randomly selected from public hospitals and who fulfilled the inclusion and exclusion criteria during the study.

### Eligibility criteria

The inclusion criteria are (1) Patients on a full TB treatment course for 1 or 2 months before the study date; (2) TB patients who can give informed consent physically and mentally and who can abide by the provided intervention with no difficulty or needing assistance; (3) Patients who can commit to the entire course of the study; (4) Patients aged 18 years or older.

The exclusion criteria are (1) Patients with a history of severe and uncontrolled psychiatric disorders; (2) Patients who are unable to read and write in Arabic; (3) TB patients not on a full TB treatment course.

### Ethics approval and informed consent

Ethical clearance for the RCT has been obtained from “Jawatankuasa Etika Universiti Untuk Penyelidikan Melibatkan Manusia” (JKEUPM) at Universiti Putra Malaysia [Ref No UPM/TNCPI/RMC/JKEUPM/(FPSK-P143]. Permission has also been obtained from the Abu Anga hospital in Sudan. The RCT will follow the ethical criteria throughout its entire procedure. Participants will be assured that their participation in the study is voluntary and that they have the full right to withdraw from the study at any time. Each participant must sign a participant consent form before the study. Data collection will be done confidentially and anonymously.

### Sample size

The sample size is calculated using the standard sample size estimate for an individually randomised design. Sample size will be determined according to the primary dependent variable (TB treatment adherence). The formula to calculate the difference between two population proportions will be used (power = 0.80, alpha = 0.05 two‐sided, P_1_ = estimated proportion (larger) P1 = 0.82, P_2_ = estimated proportion (smaller) P2 = 0.69) [22].

$$N=\frac{\{1.96\sqrt{2\times 0.33(1-0.33)}+0.842\sqrt{0.82(1-0.82)+o69(1-0.69)}{\}}^{2}}{{\left(0.82-0.69\right)}^{2}}.$$

N = 171 for each group.

By taking into account a 10% attrition rate, a total sample size of 188 (171 + 17 = 188) participants will be required for each group, giving a total sample size of 376 participants.

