#### Study outcomes

*Primary outcome*. The primary outcome of interest in this study is the treatment adherence for TB medications. The data will be collected using the Medication Adherence Rating Scale (MARS), a 10-item self-reporting instrument that describes three dimensions: medication adherence behaviours (items 1–4), attitude toward taking medication (items 5–8), as well as negative side effects and attitudes to medication (items measured 9–10) [26].

*Secondary outcomes*. The secondary outcome variables in this study include:

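### The sample size is for one binary adherence test, but the primary outcome is a 10-item score with no cut-off or primary time point, so the stated power and alpha belong to no defined primary analysis

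*Protocol article*

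**What the plan says.** The Sample size section of the protocol article states "Sample size will be determined according to the primary dependent variable (TB treatment adherence") and then "The formula to calculate the difference between two population proportions will be used". Its inputs are "power = 0.80, alpha = 0.05" (two-sided) and "P1 = 0.82, P_2_ = estimated proportion (smaller) P2 = 0.69". The result is "N = 171 for each group", raised to 188 per group and 376 in total for 10% attrition. The section does not say what makes a patient adherent, or at which assessment the two proportions are compared.

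The Study outcomes section gives the primary outcome as adherence measured by the MARS, "a 10-item self-reporting instrument that describes three dimensions". It states no scoring rule, threshold or primary time point. The secondary outcomes do have scoring: knowledge from 0 to 15, summed Likert items for health beliefs, and quality-of-life domains from 0 to 100.

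The Introduction hypothesises that "at the 1- and 4-month assessments, TB patients in the intervention group will show a raised score in the following areas", and adherence heads the list that follows. Neither assessment is ranked above the other there, in the Abstract or under Study design.

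The Statistical analysis section lists chi-square, t-test, a multivariable regression of unstated type, Cochran's Q, one-way repeated-measures ANOVA, and GEE for main effect and interaction. It sets significance at p < 0.05. None of these is named as the primary test.

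**The concern.** A power statement has meaning only for a particular outcome, time and test. Here the calculation assumes a binary outcome compared once, while the instrument and the hypothesis point to a score assessed twice after baseline. A reader cannot tell which analysis has 80% power, or which p-value is held to 5%.

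The scale, the MARS cut-off and the time point all remain open for the main claim. If they were settled after the data had been seen, the choice could decide whether the trial is reported as positive, and no later analysis could repair that convincingly.

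**Working it through.** **Inputs.** From Sample size: P1 = 0.82, P2 = 0.69, two-sided alpha 0.05 (z = 1.96), power 0.80 (z = 0.842), 171 per group. From Introduction and Study design: assessments at 1 and 4 months. Assumed, because the documents give no values: the correlation between the 1-month and 4-month tests.

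**1. The plan's own figure.** Two-proportion formula with pooled proportion (0.82 + 0.69)/2 = 0.755:

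- 1.96 × √(2 × 0.755 × 0.245) = 1.192
- 0.842 × √(0.82 × 0.18 + 0.69 × 0.31) = 0.506
- n = (1.192 + 0.506)² / 0.13² = 170.7, so 171 per group

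The figure reproduces, and power at 171 is 80.1%. The formula as printed has 0.33 in place of the pooled proportion and would give 194; that is a separate matter. The 171 is right for one binary comparison at one time, and only for that.

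**2. What the same 171 gives under other readings of the plan.**

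| Reading | Consequence |
|---|---|
| Binary, one named time | 80.1% power; 171 stands |
| Binary, either time may succeed, each at unadjusted 5% | Familywise error 9.5%, 9.1%, 8.3% at assumed correlation 0.3, 0.5, 0.7 (9.75% if independent: 1 − 0.95²) |
| Binary, either time, Bonferroni 2.5% each | 71.2% power at each time; 80% needs 207 per group, or 207/0.9 = 230 with attrition |
| Binary, both times must succeed at 5% | No inflation; joint power 64% (independent, 0.80²) to 75% (correlation 0.9), taking 80% at each time |
| Mean MARS score, one time | 80% power for (1.96 + 0.8416) × √(2/171) = 0.30 SD |
| One joint GEE contrast | No inflation; power not stated in the plan |

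The rows differ in error rate, in power or in both, and the document does not say which row applies.

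**3. The score scale.** The 0.30 SD is solved backwards from n. The documents give no MARS standard deviation and no expected mean difference, so it cannot be compared with the intended 13-point effect without a further assumption. If 82% v 69% came from cutting a normally distributed score at one threshold, the gap would be about 0.42 SD, and 90 per group would give 80% power.

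**The case against.** The strongest reply is that this is a journal article. A full protocol or analysis plan may hold the MARS cut-off, the primary contrast and the handling of two time points, and their absence here would not be an error. That stands for each item taken singly. It does not remove the conflict within the text, which sizes the trial on a proportion and then describes and hypothesises about a score. Condensing is also a weak explanation when the article scores every secondary outcome and not the primary.

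Second, a binary primary remains possible. In the Introduction's list the adherence item is worded as a level and the knowledge item as scores, and the Statistical analysis section provides for categorical data. The t-test and ANOVA have other continuous outcomes to serve. A reader might infer that the primary must be a score, or that it will be tested both ways; the text does not establish either.

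Third, a reader might infer that the plan commits to a type I error near 9%. It does not. That figure needs two separate unadjusted tests with either one sufficient, and the document never says so. The text does not call the two times co-primary, and it names GEE, which could supply a single contrast.

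Fourth, a reader might add that only items 1–4 of the MARS describe adherence behaviour, so that a change in attitude could pass for adherence. That concerns what the instrument measures and not whether the power matches the test. The module also covers treatment adherence itself and action planning.

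**Conclusion.** The mismatch is real and should be settled before outcome data are seen. The stated 80% power and two-sided 5% alpha belong to a single binary comparison that the rest of the document does not define as primary.

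Its size depends on how the gap is filled. Familywise error is about 8% to 9.5% only if either time may succeed at an unadjusted 5%, with assumed correlation 0.7 to 0.3. It stays at 5% with one GEE contrast. It is not inflated if both times are required, but joint power then falls to between 64% and 75%.

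The documents do not support saying that 171 is miscalculated for its stated inputs, that a score analysis would be underpowered, or that 0.30 SD is the planned effect. All figures at 171 per group hold only if the 376 total in Sample size is the true target and not the 146 in the Abstract. With 73 per group, power for 82% v 69% would be 44.6%.

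**What to change.** Name in the protocol one primary scale, one primary time point (for example 4 months, with 1 month secondary) or one joint GEE contrast, and one between-arm comparison adjusted for baseline MARS. Then match the power statement to that choice.

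- **If the proportion stays primary:** fix the MARS cut-off now, keep 82% v 69% with 171 per group at the named time, and do not use the t-test or ANOVA for the primary.
- **If the score is primary:** replace the two-proportion statement with the detectable difference. With 171 analysed per group, that is 80% power for about 0.30 SD, labelled as derived from n and not as the planned effect.
- **If a joint GEE contrast is primary:** state its power, with the assumed correlation between visits.

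Reconcile the 376 and 146 totals at the same time, since each version of the power statement depends on them. Reporting items 1–4 separately is an optional supportive analysis.

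The cost is protocol wording and one restated power sentence. For the proportion or the score at one time point, no patients are needed beyond the 376 in Sample size. The downside is that, if one time point is chosen, the other can no longer carry the primary claim.
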